### Intervention

During the intervention time period, pregnant women who come for their first ANC visit at the HP will receive standard individual care. At the end of this first ANC visit, eligible women who agree to participate in G-ANC will be added to the G-ANC cohort. Approximately eight to 10 women will be enrolled in a cohort. Cohort membership will be fixed (i.e., the same women and facilitators at each meeting). Two additional pregnant women who meet study criteria can be added to a G-ANC cohort if added to the cohort by the start of the second G-ANC meeting. Six monthly G-ANC meetings will be conducted for each cohort on a fixed day/time at each HP. Each cohort will meet for G-ANC meetings in a designated meeting space that is set up to ensure privacy during clinical consultations. The G-ANC meeting will be conducted by at least one HEW who is trained in the G-ANC service delivery model.

Each meeting will have the same general structure: self-assessment by the clients/peer-to-peer self-assessment initially taught and supervised by the HEW, such as measurement of weight and blood pressure using an automated cuff; individual assessments/clinical care by the HEW in a private space; discussions around pre-determined and appropriate gestational-age themes using illustrative cards and take-home booklets designed for G-ANC; and plan/reflect and peer-support activities that create group cohesion.
Table 2 presents the G-ANC meeting schedule and content per meeting. Each meeting is expected to last 90–120 minutes and will be documented as an ANC contact. Social distancing in response to COVID-19 as per national guidelines will be enforced during meetings. Women will have the opportunity for additional private time with the HEW after the G-ANC meeting if desired or needed for health and/or safety. Women will be told that they can and should return at any time if they have questions or concerns. Phone/text reminders will be used to remind participants of G-ANC meetings as a strategy to improve ANC attendance.

**Table 2. T2:** G-ANC intervention meeting schedule.

Meetings	Timing (gestational age)	Theme/Meeting Plan
Meeting 1	4–5 months	• Introduction to group care • Preventing problems in pregnancy • Teach self-assessments
Meeting 2	5–6 months	Danger signs during pregnancy • Sexually transmitted infection (STI) transmission and partner communication/negotiation

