### Outcomes

**
*Primary outcome 1*:** Proportion of women with at least four ANC visits.

**
*Primary outcome 2*:** Proportion of women who delivered in a health facility.

After exploring the balance by time period/intervention status and correlations, the effect of G-ANC will be estimated using generalized linear mixed effects models with binomial distribution and logit-link.

We will adjust for facility- and individual-level characteristics that show imbalance between the intervention versus control time periods and can be strongly correlated with the outcome scores. The primary analysis will not adjust for multiplicity and will be performed at 0.05 level of statistical significance.

**
*Secondary outcomes*:** Satisfaction level of women with ANC services, proportion of women who reported self-efficacy or empowerment.

Analysis of secondary outcome measures will follow a plan similar to the analysis of the primary outcome. Subgroup analysis will be conducted for specific subgroups to determine if the interventions were different. The key subgroups of interest are marital status, education, and economic status.

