### Sample size

We used the existing data from Amhara region for two primary study outcomes (i.e., four or more ANC contacts [31.5%] and facility-based delivery [27.1%]) to calculate the number of clusters (i.e., HCs) to be randomized to be able to detect an odds ratio of 2 comparing post-intervention to pre-intervention proportion with 80% statistical power using stepped-wedge design with three time periods and two steps for switching from standard care to intervention (
Figure 1). For the complete stepped-wedge design, the calculations indicate that a sample of 12 HCs with three time periods/two steps, six HCs switching from control to treatment at each step, and with an average of 30 women per cluster (i.e., three HPs with 10 women in each) per time period achieves 84% power to detect an odds ratio of 2 at 0.05 level of statistical significance. The underlying pre-intervention proportions and the post-intervention proportions associated with odds ratio of 2 are shown in
Table 4.

**Table 4. T4:** Pre-intervention and post-intervention proportions with associated odds ratio.

Study Outcome	Pre-Intervention Proportion, P2 ( Table 1)	Odds Ratio to be Detected	Post-Intervention Proportion, P1
Four or more ANC contacts	0.315 (Amhara)	2	0.48
Facility-based delivery	0.271 (Amhara)	2	0.43

The within-HC correlation (intraclass correlation coefficient [ICC]) is assumed to be 0.100. This level of correlation is consistent with the one reported by Ousman
*et al.*, where clustering was done at enumeration-area level with an ICC of 0.11 for ANC visits (
Ousman *et al.*, 2019). The total sample size for ANC clients is then 12 HCs x 3 HPs x 10 women/HP x two time periods = 720 women. An odds ratio of 2.0 translates to 50%–60% improvement in completion of four or more ANC contacts and 60%–70% improvement in facility-based delivery in the G-ANC arm compared to pre-intervention.

The study will be conducted in 12 HCs. The overall sample size is a total of 770 women. The pilot will enroll 50 women (i.e., 10 women per HP, five HPs), and the randomized control trials will include a maximum of 720 women (
Table 5). Sample size for the qualitative data collection is indicated in
Table 6.

**Table 5. T5:** Number of HCs, HPs, and women included in the G-ANC study.

	Pilot	Time parried 1 Control	Time Period 2 (control + intervention)	Time Period 3 (intervention)	Total
HC	2	6	12	6	**14**
HP	5	18	36	18	**41**
Women	50	180	360	180	**770**

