### Data analysis

**
*Quantitative data analysis.*
** Data analysis and the reporting of results for this study will be conducted in accordance with norms for analyzing cluster randomized trials as described in the Consolidated Standards of Reporting Trials guidelines with considerations for the step-wedge extension (
Hemming *et al.*, 2018;
Hemming *et al.*, 2019). If there is variation within the clusters, the statistical analysis will be adjusted based on the pollution levels. The primary analysis will be conducted using intention-to-treat analysis. After exploring balance by time period/intervention status and correlations, the effect of G-ANC will be estimated using generalized linear mixed effects models with binomial distribution and logit-link. The model will include G-ANC as the intervention indicator, time period and their interaction as the primary predictors, and HC as the random intercept. We will adjust for facility- and individual-level characteristics that show imbalance between the intervention vs. control time periods and can be strongly correlated with the outcome scores. The primary outcomes will be compared across time periods both within the intervention and control groups. Comparisons will be made within a given time period (e.g., T1, T2, and T3) for both the intervention and control conditions. The amount of missing data will be assessed for each variable and overall, for the sample. If more than 5% of data on covariates are missing, multiple imputation procedures will be used assuming data are missing at random (
Sterne *et al.*, 2009).

**
*Qualitative data analysis*.** Following each audio recording, either the moderator or an official transcriber familiar with local language and English will transcribe from the audio recording. Analysis will be thematic content analysis with similar themes and subthemes. Coding of textual passages will be done using open code 4.03 Umeå: Umeå University, an open-source tool known for qualitative analysis.

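### With a health-center intercept as the only random effect and an effect resting on 6 versus 6 centers, a default Wald fit would run the 0.05 tests at about 8-12%

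*Protocol article*

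**What the plan says.** The Data analysis section gives the primary model in one sentence: "The model will include G-ANC as the intervention indicator, time period and their interaction as the primary predictors, and HC as the random intercept". The only random term in it is the last one named, "and HC as the random intercept". The Outcomes section sets the test level: "The primary analysis will not adjust for multiplicity and will be performed at 0.05 level of statistical significance". The protocol names no estimation method, reference distribution (z or t) or small-sample correction. One sentence in Data analysis promises some adjustment for variation within clusters, but its wording is unclear and it names no model term.

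On the design, Sample size says "The study will be conducted in 12 HCs" and bases the power on a complete wedge, "a sample of 12 HCs with three time periods/two steps, six HCs switching from control to treatment at each step", "with an average of 30 women per cluster (i.e., three HPs with 10 women in each) per time period". The data to be collected are fewer: "12 HCs x 3 HPs x 10 women/HP x two time periods = 720 women". Table 5 and the Trial phase text show that the first six HCs give control data at T1 and G-ANC data at T2, and the other six give control data at T2 and G-ANC data at T3. The within-HC ICC is 0.100. No between-period correlation and no health-post or cohort ICC is given.

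**The concern.** A single HC intercept says that two women from the same HC are equally correlated whether they were enrolled in the same period or in different ones. Each period enrolls new women, the HCs span five districts, and corrective measures are expected between blocks. HC-specific change over time is therefore plausible, and the model has nowhere to put it. The G-ANC arm has a further level: "Cohort membership will be fixed (i.e., the same women and facilitators at each meeting", with one group per health post.

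The number of clusters is the second issue. T1 is all control and T3 is all G-ANC, so their data go into estimating their own period effects. The treatment effect is left to 12 HCs at T2. Maximum likelihood underestimates a between-cluster variance based on so few clusters, and a normal reference then ignores that the variance was estimated. Intervals would be too narrow and a policy decision on G-ANC would carry more false-positive risk than the stated 0.05.

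**Working it through.** **Inputs from the protocol.** 12 HCs, 6 per sequence; 30 women per HC and period; two periods per HC; ICC 0.10; control proportions 0.315 (ANC visits) and 0.271 (facility delivery); level 0.05. Assumed: two-sided tests, and cluster autocorrelation (the share of HC variance common to both periods) of 1, 0.9, 0.8 or 0.5.

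**The plan's own figure.** The Hussey-Hughes formula for the complete wedge, with total variance 0.315 x 0.685 = 0.2158 split 10:90 between and within HCs and a difference of 0.479 - 0.315 = 0.164, gives power of 83.9% (83.1% for facility delivery). The stated 84% reproduces, but for 12 x 3 x 30 = 1,080 women.

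**What identifies the effect.** The 720-woman design has four condition-by-period cells: T1 control, T2 control, T2 G-ANC and T3 G-ANC. An intercept, two period effects and one treatment effect use all four. Adding the interaction gives six columns of rank four, so it cannot be estimated and was dropped below. The remaining estimate is the T2 contrast.

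**Hand check on the logit scale.** HC variance = (0.1/0.9) x pi^2/3 = 0.3655. Binomial variance = 1/(30 x 0.2158) = 0.1545. Standard error (SE) of the contrast = sqrt[(1/6 + 1/6) x (0.3655 + 0.1545)] = sqrt(0.1733) = 0.416. Maximum likelihood shrinks the variance by about 10/12, so the SE becomes about 0.416 x 0.913 = 0.380. P(|t10| > 1.96) = 7.8% from the z reference alone, and 10.4% with that shrinkage.

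**Simulation under no effect.** The stated model was fitted by Gauss-Hermite maximum likelihood with 2,000 trials per row (Monte Carlo error about 0.6 points).

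| Assumed truth | p | Empirical SD | Mean model SE | Wald z | t, 10 df |
|---|---|---|---|---|---|
| HC only | 0.315 | 0.427 | 0.386 | 9.0% | 5.4% |
| HC only | 0.271 | 0.422 | 0.392 | 8.3% | 5.1% |
| Autocorrelation 0.9 | 0.315 | 0.409 | 0.379 | 8.4% | 4.7% |
| Autocorrelation 0.9 | 0.271 | 0.426 | 0.386 | 8.0% | 5.2% |
| Autocorrelation 0.8 | 0.315 | 0.424 | 0.373 | 9.5% | 6.0% |
| Autocorrelation 0.8 | 0.271 | 0.432 | 0.382 | 9.0% | 5.2% |
| Autocorrelation 0.5 | 0.315 | 0.419 | 0.348 | 11.2% | 6.7% |
| Autocorrelation 0.5 | 0.271 | 0.438 | 0.353 | 12.2% | 8.5% |
| HC + health-post variance | 0.315 | 0.440 | 0.399 | 8.7% | 5.1% |
| HC + health-post-by-period variance | 0.315 | 0.421 | 0.389 | 8.5% | 4.8% |

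The SE shortfall is 1 - mean SE/SD. For HC only it is 1 - 0.386/0.427 = 10% and 1 - 0.392/0.422 = 7%. At 0.8 it is 12% for both outcomes. At 0.5 it is 1 - 0.348/0.419 = 17% and 1 - 0.353/0.438 = 19%. The true spread hardly changes between rows, but the single intercept picks up less of it as autocorrelation falls.

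A repeat with 2,500 trials gave z rates of 8.3%, 9.9% and 11.9% (autocorrelation 1, 0.8, 0.5) and t rates of 5.4%, 6.8% and 8.0%. Adding both health-post and intervention-only group variance gave 9.4% with z and 5.6% with t. A further simulation of 1,200 trials per scenario gave z rates of 8.8%, 9.8% and 11.2%.

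**Comparator.** A t-test on the 12 HC proportions at T2 held 4.5-5.7% in five scenarios, so the excess can be avoided.

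**The case against.** The strongest objection is that the protocol never chooses Wald z. Estimator, reference distribution and small-sample correction are commonly left to the SAP, which is not shown. This stands. A reader might infer that the trial's tests will run at 8-12%; the document supports only that they would under a default fit.

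A reader might also blame the missing health-post and cohort terms. The figures do not support that. With the HC-only structure exactly right the rate is already 8-9%, and health-post or group variance leaves it at about 8.5-10%. Nor do the documents establish HC-by-period variance: a shift common to all HCs is absorbed by the period effects, and no autocorrelation is reported.

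The rates also depend on the data collected. If the first 18 health posts take up the optional second cohort at T3, one check with Wald z gave 5.7% under HC-only truth but 11.3% at autocorrelation 0.8. In the complete wedge used for the power calculation, the stated model is near nominal under HC-only truth (5.4-5.9%) but reaches 16-18% at 0.5, and 10.6-12.8% even with t on 10 df. A small-sample reference alone therefore does not always rescue the single-intercept structure.

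Finally, a reader might fold in the two unadjusted primary outcomes and quote a combined error rate. The protocol discloses that choice openly. It is debatable on its own terms and is not part of this point.

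**Conclusion.** The point holds in conditional form. For 12 HCs, two periods each and ICC 0.10, the stated random-effects structure with maximum likelihood and a normal reference gives SEs about 7-10% too small and a true level of about 8-9% when the structure is correct. The level is about 9-10% at autocorrelation 0.8 and 11-12% at 0.5, with SEs up to 19% too small. With t on 10 df it is about 5-7%, except about 7-8% at 0.5.

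This rests on three assumptions: no small-sample provision in the unseen SAP, the interaction dropped, and no second cohort at T3. It also takes the 12 HCs of the Sample size section rather than the six in the abstract. The direction is well supported; the upper part of the range depends on autocorrelation values that the documents do not give. It is a cheap improvement to the analysis wording, not a proven failure of the trial.

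**What to change.** In Data analysis, replace the single HC intercept with random effects for HC and HC-by-period, and put a health-post or cohort term in a sensitivity analysis. State that p-values and confidence intervals use a small-sample method (t with about 10 df, or a Kenward-Roger type correction) or a permutation test over the stratified HC randomization. If the SAP already says this, a cross-reference is enough. Remove the G-ANC-by-period interaction from the primary model, since the collected cells cannot estimate it.

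Two cautions. The enlarged model was not itself simulated, and with 12 HCs and binary outcomes a variance component may be estimated at zero, so name a fallback such as the cluster-level comparison at T2. Before choosing a permutation test, count the allocations that the stratified scheme permits, because too few would limit the attainable p-values.

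The change needs no new data. The price is somewhat wider intervals and lower power, in a design where the plan's own formula gives only about 30-40% for the 720 women (for ANC visits: SE = sqrt[(1/3) x (0.0216 + 0.1942/30)] = 0.097; 0.164/0.097 = 1.70; power about 40%).

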**Pregnant women (ANC clients)**	Inclusion criteria	• Minimum age of 15 years at the time of enrollment; pregnant 15–17-year-olds will be treated as emancipated/mature as per local regulations • Gestational age ≤ 20 weeks at the time of enrollment determined by last menstrual period, pelvic exam, fundal height, quickening, ultrasound, and/or timing of fetal heart tones and pregnancy test* • Able and willing to provide adequate locator information • Planning to reside at their current location for at least 10 months • Agree to participate in the study and continue ANC at HP • Willing to participate and consent to follow-up for up to six weeks post-delivery • Willing to receive G-ANC at the HP level (during the intervention period)
	Exclusion criteria	• Plan to travel away from the study site for more than four consecutive weeks during ANC or before six weeks post-delivery • Unable to provide consent • Have any condition that, in the opinion of the investigator or designee, would complicate interpretation of study outcome data or otherwise interfere with achieving the study objectives

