**: During time period one (T1: control period), two HEWs will be trained on community mobilization and gestational age estimation (including knowledge and skills) at selected HP for two days. During the intervention period, two HEWs per HP from intervention HP will be trained on G-ANC facilitation, gestational age estimation, and community mobilization for five days. From control HPs, two HEWs per HP will be trained on community mobilization and gestational age estimation for two days. Midwives from intervention HCs who will provide on-site mentorship to HEWs during G-ANC implementation will be trained for four days on G-ANC-focused mentorship by the study team (i.e., senior health professionals from Jhpiego Ethiopia with specialization in maternal health). Midwives from control HCs will be oriented for one half day on community mobilization, screening procedures, and linking women who come to the HC for their first ANC visit to HPs under their catchment. Key stakeholders, including participating health facility managers and regional managers, will be oriented to G-ANC to build ownership and support. Midwives from HC will provide mentorship, supervision, on-the-job support, guidance, and feedback to HEW as they implement G-ANC in their HPs.

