For HEWs and health facility managers, study staff will explain the purpose based on the inclusion criteria. The HEWs will be oriented to the study including the randomization (they will not be blinded to the order of randomization of their HC and affiliated HPs) and their role in the study including screening first-time ANC clients for eligibility to participate. HEWs who will be facilitating G-ANC meetings will be informed that they may be asked to participate in an in-depth interview (IDI) at the end of the study related to implementation of group-based care and its effect on their job and satisfaction levels. Oral consent will be obtained in a private location at the health facility by research assistants.

For the regional health managers, study staff will contact the regional health bureau responsible for overseeing reproductive health programs in the Amhara region via phone or in-person and invite the regional health manager to participate in an IDI as per the inclusion criteria. An appointment will be scheduled to obtain informed consent and conduct the IDI, preferably at the regional health bureau office. Written consent will be obtained by the research assistant who will conduct the interview in a private location.

For the IDIs of women and HEWs involved in G-ANC, qualitative data will be collected at the end of the study after all G-ANC meetings have been conducted. Oral consent will be obtained from the HEWs and eligible women three to six months postpartum to be enrolled in the qualitative portion of the study.

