### Randomization

Health centers with catchment HPs that provide POCT for ANC services will be listed and randomized to begin the intervention at T2 (i.e., the first randomized set of facilities) or T3 (i.e., the second randomized set of facilities). These facilities will be randomized 1:1 before T1 to two different intervention start times (i.e. two sequences), stratified by location and client volume, using randomly permuted blocks of size 2 and 4. We will use centralized randomization as the allocation concealment mechanism. A remote and independent statistician in the Johns Hopkins Bloomberg School of Public Health (JHSPH) will generate and implement the allocation sequence, and communicate it to the study sites after confirming the eligibility of the clusters. Health extension workers will identify pregnant women and provide the list of women to Addis Continental Institute of Public Health (ACIPH). ACIPH field workers will take consent and enroll eligible women.

**
*Blinding*:** Study staff and those assessing outcomes will not be blinded to knowing the study time period to which facility is randomized. The participants will also not be blinded about the type of care they will be receiving (G-ANC or routine/conventional care).

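### Covariates for the primary models are picked after seeing imbalance and outcome correlation, so adjustment of primary outcome 1 for gestational age at enrolment depends on how the rule is read; it should be prespecified

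*Protocol article*

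**What the plan says.** The Data analysis section sets the order of work: "After exploring balance by time period/intervention status and correlations, the effect of G-ANC will be estimated". It names the terms of the mixed logistic model as G-ANC, time period, their interaction and a health-centre random intercept. Further covariates are added by rule: "We will adjust for facility- and individual-level characteristics that show imbalance between the intervention vs. control time periods and can be strongly correlated". The correlation meant is that between covariate and outcome. The Outcomes section repeats the rule directly after the two primary outcomes: "We will adjust for facility- and individual-level characteristics that show imbalance between the intervention versus control time periods". Neither place gives a threshold or names a covariate.

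On enrolment, Table 1 admits women at "Gestational age ≤ 20 weeks at the time of enrollment". The Randomization section allocates health centres before T1, stratified by location and client volume, and then says "Health extension workers will identify pregnant women and provide the list of women". Of these workers, Recruitment and consent states that "they will not be blinded to the order of randomization of their HC and affiliated HPs".

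**The concern.** This is a stated method, not detail left to an analysis plan. The covariate set of the primary model depends on observed associations with the outcome, in a trial where staff and outcome assessors are unblinded.

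Gestational age at enrolment is where this matters most. Primary outcome 1 is a visit count crossing a threshold, so a woman enrolled at 10 weeks has more time to reach it than one enrolled at 20. Women are found after allocation by workers who know it, so chance is not the only thing that could separate the conditions on this variable. If intervention women enrolled earlier and the model did not adjust, part of that difference would appear as an effect of group care. The rule may or may not adjust, because "can be strongly correlated with the outcome scores" can be read in several ways.

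**Working it through.** The plan gives no figure for covariate choice. The benchmark is its target effect for primary outcome 1 (Sample size, Table 4). Control proportion 0.315 has odds 0.315/0.685 = 0.460. Doubled, that is 0.920, and 0.920/1.920 = 0.479, which matches the stated 0.48. The target is 16.5 points, or ln 2 = 0.693 on the log-odds scale.

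**1. Size of a shift left wholly uncorrected.** Assumptions, not in the protocol: one visit by enrolment; later visits at a constant weekly rate λ until 40 weeks; success means at least 3 later visits; no true effect; λ set so that mean success is 0.315. Enrolment age is uniform on 4–20, 8–20 or 12–20 weeks. Later visits are Poisson or negative binomial (size 2). A shift moves the whole intervention distribution earlier.

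Worked case (Poisson, 8–20 weeks, λ = 0.0757):
- Enrolled at 8 weeks: mean 0.0757 × 32 = 2.42 later visits, P(≥3) = 0.436.
- Enrolled at 20 weeks: mean 0.0757 × 20 = 1.51, P(≥3) = 0.195.
- One-week shift: average success rises from 0.315 to 0.335, odds ratio (0.3351/0.6649)/(0.315/0.685) = 1.096.

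Range over the six models:

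| Shift | Odds ratio | Points | Share of ln 2 |
|---|---|---|---|
| 0.5 week | 1.03–1.05 | 0.7–1.1 | 4–7% |
| 1 week | 1.06–1.11 | 1.3–2.2 | 9–14% |
| 2 weeks | 1.13–1.22 | 2.6–4.4 | 17–28% |

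If visits are instead monthly opportunities, each attended with the same probability, the odds ratios are 1.10–1.13 (1 week) and 1.22–1.27 (2 weeks).

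**2. Would the rule pick it up?** In the six models, the correlation of enrolment age with success is -0.08 to -0.19 (-0.14 to -0.22 with monthly opportunities). Many analysts would not call that strong.

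A separate null simulation used the planned 720-woman layout, with 3000 runs per setting. It assumed gestational age with mean 16 weeks and SD 2.5, capped at 20; a log-odds effect of 0.3 to 0.9 per SD; and eight other weak covariates. Share of trials in which gestational age enters the model:

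| Reading of the rule | No shift | 0.5 week | 1 week |
|---|---|---|---|
| p < 0.05 for both imbalance and correlation | 16–17% | 62–68% | 90–99% |
| standardised difference > 0.1 and absolute correlation > 0.2 | 0.7–35% | 2–80% | 3–99% |

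**3. Effect on bias and error, same simulation.**
- Gestational age never adjusted for, shift 0.5–1 week: risk difference biased by +1.2 to +6.9 points, null rejection 4.8–14.8%.
- Gestational age prespecified: bias about 0, rejection 4.3–6.5% over all settings.
- One fixed selection rule (p < 0.05 for both): bias at most about 0.3 points, rejection 4.3–5.6%.
- Seven readings of the rule compared: the estimate moves 1.3–3.0 points on average, and the chance that at least one is significant is 5.7–7.8%.

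**4. Precision.** With 12 centres × 30 women × 2 periods, the Poisson model, and a logistic GEE standing in for the mixed model (600 runs per shift), adding enrolment age moved the odds ratio from 1.087 to 0.996 (1 week) and from 1.194 to 1.004 (2 weeks). The SD of the log odds ratio went from 0.394 to 0.405 and from 0.392 to 0.402, a loss of 2–3%. On the risk-difference scale in the other simulation, the standard error was 0.94–0.99 of the unadjusted one.

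**The case against.** The strongest reply is that the odds ratios describe a plan that never corrects, whereas this plan usually would. That stands. The uncorrected bias is also small against the trial's own noise: ln(1.087)/0.394 = 0.21 standard errors at 1 week and ln(1.194)/0.392 = 0.45 at 2 weeks. By normal approximation, null rejection would be about 5.5% and 7.4%.

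A reader might infer that recruitment did bias the trial. The documents do not support that. They report no shift, and the direction of any shift is open, since groups are formed from women of similar gestational age. There are safeguards: the 20-week cap applies to both conditions, all new attendees are screened, field workers of the research institute take consent and enrol, and "From control HPs, two HEWs per HP will be trained on community mobilization and gestational age estimation for two days". A reader might also infer that selecting covariates inflates the type I error materially. With one fixed rule, the simulation does not show it.

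A further objection is over-adjustment. The Intervention section says the model is meant to increase early entry, and if it does, adjustment removes part of its effect. This is largely met: each woman joins the group only after a first individual visit, so her enrolment age precedes her group care. Mobilisation could still act earlier, so the estimate without gestational age is needed as well.

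Finally, replacing the whole rule with gestational age alone would drop adjustment for other characteristics in a trial of 12 clusters. That is right, and the fix below avoids it.

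**Conclusion.** The concern holds as a modest design point, worth considering but not a demonstrated bias. The protocol fixes an outcome-dependent covariate rule without thresholds. Under reasonable readings, a prognostic variable already determined for eligibility may be left out of the model for primary outcome 1.

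The spurious odds ratio of about 1.06 to 1.22 for an uncorrected 1 to 2 week shift (up to 1.27 with monthly opportunities) is an upper limit for the plan as written. It rests on assumed visit patterns and a hypothetical shift towards earlier entry. The simulations also treat gestational age as error-free, although Table 1 allows several dating methods. Women linked from a health centre had their first visit before enrolment, so enrolment age only approximates entry age for them. What remains is residual bias from a moderate imbalance that the rule might miss, and a primary model settled after outcome correlations are seen.

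**What to change.** Before T3 data are analysed, and preferably before anyone examines gestational age by condition:

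- Prespecify gestational age at enrolment as a fixed covariate in the model for primary outcome 1, together with the stratifiers (location, client volume).
- Move adjustment for other characteristics found imbalanced to a sensitivity analysis.
- Report the distribution of gestational age by condition and period.
- Report the estimate without gestational age alongside the primary one.

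Study status says the T1 and T2 surveys are done (180 + 360 = 540 of 720 planned women), so the change should be dated and should state what had already been seen.

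The cost is a short change to the analysis text, variables already collected, one table row and two extra estimates. Eligibility, recruitment and sample size do not change. The simulated precision loss from gestational age is 2–3% on the log-odds scale; the stratifier terms were not simulated. The small downside is that adjustment could remove any part of the effect that works through earlier entry, which the estimate without gestational age would show.
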